### Sample size

The sample size was determined to detect a between-group difference in the primary outcome (general CLIMBS latent factor score) using a two-sided test of mean differences (α = .05, power = 90%). Assuming a standardized mean difference of g = 0.3 [13], approximately 260 participants per arm are required. Inflating this by 30% to account for expected attrition in behavioural trials resulted in a recruitment target of approximately 680 participants. Sensitivity analyses indicate adequate power for effects in the range g = 0.30–0.40.

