### Statistical methods

The principal analyses will follow an intent-to-treat statistical analysis plan.

Patterns and extent of missing data will be examined descriptively, including proportions of missingness per variable and associations with observed participant characteristics. CLIMBS item-level missingness will be handled directly within the graded response IRT framework using marginal maximum likelihood estimation, which accommodates incomplete response patterns under the assumption of missing at random (MAR). No imputation of item responses is planned. If missingness in covariates or outcome data exceeds trivial levels, appropriate model-based methods consistent with the assumed missingness mechanism will be applied.

CLIMBS will be analysed using a bifactor graded response IRT model to obtain a general mitigation behaviour score on a common metric across trial arms and assessment waves. Item parameters will be estimated jointly (not separately by arm). Intervention effects will be tested using mixed-effects models with participant-level random intercepts (or equivalent marginal approaches) to account for within-person correlation over repeated assessments. The primary analyses will use the general factor CLIMBS score as the dependent variable. Sensitivity analyses using the unit-weighted total score will be conducted to assess robustness of findings. All randomized participants will be included in regression analyses, with separate analyses for all continuous primary and secondary outcomes and time and group as predictor variables. Between-group effect sizes at the primary endpoint will be estimated using Cohen’s *d*. In addition, a Complier Average Causal Effect (CACE) analysis will be conducted to estimate the causal effect of the intervention among participants who complied with their assignment (“compliers”). The original randomization will be used as an instrumental variable to account for potential bias due to selective participation. The CACE will be estimated using two-stage least squares (2SLS) regression with the CLIMBS general factor as the outcome. This analysis will be reported as a secondary, complementary analysis. The naturalistic follow-up (1, 3 and 6 months) will be analysed as within-group regression analyses in the intervention group, to test for maintenance of intervention effects on all outcome measures.

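### The CACE is specified as 2SLS with no baseline covariate and no stated handling of missing week-5 scores; adding baseline CLIMBS and a missing-data sensitivity analysis would be a minor improvement

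*Protocol article*

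**What the plan says.** All of this is in the protocol article, mainly under Statistical methods.

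- Estimator and outcome: "The CACE will be estimated using two-stage least squares (2SLS) regression with the CLIMBS general factor as the outcome".
- Instrument and purpose: "The original randomization will be used as an instrumental variable to account for potential bias due to selective participation".
- Status: "This analysis will be reported as a secondary, complementary analysis".
- Missing items: "CLIMBS item-level missingness will be handled directly within the graded response IRT framework using marginal maximum likelihood estimation". This concerns unanswered items within a questionnaire, under missing at random (MAR).
- Missing outcomes in general: "If missingness in covariates or outcome data exceeds trivial levels, appropriate model-based methods consistent with the assumed missingness mechanism will be applied". No method is named and the CACE is not mentioned.
- Analysis set: "All randomized participants will be included in regression analyses". The sentence goes on to describe models with time and group as predictors; the CACE is introduced afterwards as an additional analysis.
- Expected loss, under Sample size: "Inflating this by 30% to account for expected attrition in behavioural trials".

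Under Outcomes, the number of completed modules is an acceptability measure collected during the intervention, not at the week-5 questionnaire. Under Waitlist control condition, the control group sees only an information page, and under Study design it is offered the course after the primary endpoint.

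**The concern.** The mixed model for the main analysis can use a participant who has only a baseline score. A 2SLS regression of the week-5 score cannot: without an outcome the record drops out. Taken literally, the CACE would therefore run on week-5 responders only.

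In the intervention arm, people who abandon the modules may well be the ones who skip the week-5 questionnaire. Waitlist participants have no modules to abandon and have a reason to stay, namely access to the course. The responders in the intervention arm could then hold a larger share of compliers than the responders in the control arm. Where that happens, the arms being compared are no longer balanced on complier type, and randomisation is not a clean instrument in the analysed set. The analysis is meant to deal with selective participation, so selection should not come back through the outcome data.

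**Working it through.** **The plan's own figure.** 260 × 1.3 = 338 per arm, 676 in total, which agrees with the target of about 680. The article gives no compliance rate, response rate by compliance, or expected CACE. Everything below except N = 694 (Study status and timeline) is therefore assumed.

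**Formula.** Nobody in the control arm has the course before week 5. Let τ be the effect in compliers and D the complier minus non-complier difference in untreated CLIMBS. Let p1 and p0 be the complier shares among week-5 responders in the intervention and control arms. Relative to the non-complier mean:

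- intervention responders: p1 × (D + τ)
- control responders: p0 × D
- 2SLS without covariates = [p1 × τ + (p1 − p0) × D] / p1 = τ + D × (p1 − p0) / p1

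The bias is D × (p1 − p0) / p1. It needs both D ≠ 0 and p1 ≠ p0. Observed compliance p1 can exceed true compliance without any bias, because numerator and denominator come from the same responders.

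**Illustration.** Assume 60% compliers, τ = 0.40 SD, and week-5 response in the intervention arm of 90% in compliers and 40% in non-compliers.

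- Overall response = 0.6 × 0.9 + 0.4 × 0.4 = 0.70
- p1 = 0.54 / 0.70 = 0.771
- Control response unrelated to type: p0 = 0.60, so bias = D × (0.771 − 0.600) / 0.771 = 0.222 × D

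The second and third columns are simulated complete-case 2SLS (2 million participants). Baseline CLIMBS is assumed to correlate 0.6 with week 5 and to carry the same difference D.

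| D (SD) | τ + bias, by formula | 2SLS, no covariate | 2SLS with baseline CLIMBS |
|---|---|---|---|
| −0.2 | 0.356 | 0.36 | 0.38 |
| 0 | 0.400 | 0.40 | 0.40 |
| 0.2 | 0.444 | 0.44–0.45 | 0.42 |
| 0.3 | 0.467 | 0.47 | 0.43 |
| 0.5 | 0.511 | 0.51 | 0.44 |

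**Same response by type in both arms.** Then p0 = p1 = 0.771 and the bias is 0 for every D. Simulation gives about 0.40 with or without the covariate, although observed compliance is 77% against a true 60%.

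**Other inputs.** With true compliance of 40% to 70%, complier response of 90% to 95%, 30% missing overall and control response unrelated to type, observed compliance runs from 51% to 95%. The bias runs from −0.053 to +0.105 SD for D from −0.2 to 0.4. If the 30% inflation is read as a multiplier, response is 1/1.3 = 77%. With complier response still 90%, the factor falls to 1 − 0.769/0.9 = 0.145, giving +0.03 to +0.07 for D from 0.2 to 0.5.

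**Precision.** At N = 694 and D = 0.3, the simulated standard error of the 2SLS estimate is about 0.12 without baseline CLIMBS and about 0.095 with it.

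**Imputation by arm.** Imputing week-5 CLIMBS from baseline and, in the intervention arm, compliance recovers 0.40 when control response is unrelated to type. When both arms share the same pattern by type, it gives 0.34 to 0.38 for D from 0.5 to 0.2, where complete-case 2SLS was unbiased.

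**The case against.** The strongest reply is that the article nowhere restricts the 2SLS to observed scores or rules out covariates. Its missing-outcome provision is not limited to the main model, and the expected attrition would trigger it. Weighting, imputation or a likelihood-based CACE could each count as model-based, and the choice may sit in an analysis plan that is not shown. This stands. A reader might infer that the plan commits to an unadjusted complete-case 2SLS; the text does not say so. What remains is that the estimator is named and the provision is not tied to it.

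A reader might also infer that inflated compliance among responders biases the CACE. It does not do so alone, as the formula shows.

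A third tempting reading is that the main analysis is sound and only the CACE is exposed. The same scenario does not support that. Response there depends on complier type, which is not a predictor in the main model. A baseline-adjusted complete-case comparison of arms, used as a stand-in for the mixed model, gives 0.32 to 0.34 against a true intention-to-treat effect of 0.6 × 0.40 = 0.24 (D from 0.2 to 0.5). Differential dropout would affect the whole trial.

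Finally, at D = 0.3 the bias (0.07 unadjusted, 0.03 adjusted) is below one standard error, and the analysis is labelled secondary. That is a fair limit on how much weight the point can carry.

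**Conclusion.** The point holds as a minor improvement. The article names 2SLS without a baseline covariate and does not say how participants without a week-5 score enter it. Under the assumed inputs, complete-case 2SLS gives 0.44 to 0.51 against a true 0.40 for D of 0.2 to 0.5 SD, and 0.36 for D of −0.2. This rests on two conditions for which the documents give no figures: response by complier type that differs between arms, and a complier/non-complier difference in untreated CLIMBS. Without either one there is no bias. A waitlist makes the first plausible but does not establish it.

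The case for the baseline covariate does not depend on those conditions. It uses data already collected, improves precision, and in every scenario tried it either reduced the bias or left it near zero. No primary conclusion depends on this analysis.

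**What to change.** 1. Include baseline CLIMBS as an exogenous covariate in both stages of the 2SLS.
2. Report compliance among everyone randomised to the intervention, from the module-completion data, next to compliance among week-5 responders.
3. State how participants without a week-5 CLIMBS score are handled. Keep the baseline-adjusted complete-case 2SLS and show beside it a sensitivity analysis that imputes or weights for missing week-5 scores, using baseline CLIMBS and modules completed. It should not replace the 2SLS: the two rest on different missingness assumptions, and each can be biased where the other is not.

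The cost is a few sentences of analysis-plan wording and slightly more analysis work, with no new data. Data collection is scheduled to finish in April 2026; the wording should be fixed before outcomes are compared by arm.

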### Aims

Considering the available evidence, it seems timely to develop and rigorously test a scalable, internet-delivered intervention targeting individual CCMBs. Our interdisciplinary team has developed an intervention, called ‘Sustainable Choices’, which innovatively combines well-established behavioural change principles and climate science. If ‘Sustainable Choices’ is proven effective at increasing CCMBs, it could be made broadly accessible to the public and thus contribute to meaningful reductions in GHG emissions, facilitate sustainable lifestyles, and improve the overall well-being of individuals on a larger scale. The primary aim of the project is to test whether ‘Sustainable Choices’ is effective in promoting CCMBs, compared to the control group. Secondary aims include exploring whether the intervention is effective in promoting psychological well-being, compared to the control group, whether the intervention acceptable for participants, and whether the effects of the intervention are maintained up to 6 months after the end of the intervention.

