## Methods

### Study design

The design of this study is a RCT where participants are allocated (1:1) to an intervention, ‘Sustainable Choices’, or a waitlist control condition for a period of 5 weeks. The primary endpoint for analyses at post-intervention (after 5 weeks). Participants in the control condition are offered to cross-over to the intervention after the primary endpoint. Naturalistic follow-up assessments will be performed 1, 3, and 6 months after the primary endpoint. The trial results will be reported according to CONSORT standards for RCTs [18]. Fig 1 describes the flow of participants with all assessment points.

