### Study status and timeline

Ethical approval for the study has been obtained from the Swedish Ethical Review Authority (reference number 2025-03308-01). The first version of this study protocol was submitted in August 2025. Participant recruitment started on 1^st^ of September 2025 and was completed 19^th^ of September 2025 (N = 694). Data collection is scheduled to be completed in April 2026.

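### The follow-up analysis is called a test of maintained intervention effects, but one arm without a comparator can only describe whether scores persist

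*Protocol article*

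**What the plan says.** The Aims section lists among the secondary aims "whether the effects of the intervention are maintained up to 6 months after the end of the intervention". The Study design section states that "Participants in the control condition are offered to cross-over to the intervention after the primary endpoint" and that "Naturalistic follow-up assessments will be performed 1, 3, and 6 months after the primary endpoint". The Statistical methods section says that these follow-up data "will be analysed as within-group regression analyses in the intervention group, to test for maintenance of intervention effects on all outcome measures".

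The same section tests intervention effects with models that have time and group as predictors, and names a between-group effect size only for the primary endpoint. The Limitations section mentions the follow-up only for its half-year length. It discusses the waitlist only for expectancy and unspecific effects, and does not mention that the comparator is lost after week 5.

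**The concern.** In this trial an intervention effect is a difference between randomised arms. To say that it is maintained at 6 months is to say something about that difference at 6 months. Once the waitlist arm has been offered the course, the difference can no longer be estimated against untreated participants, yet the plan says that a regression in one arm will test it.

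At stake is a published durability claim, on the primary outcome and every secondary outcome, that the design cannot support. The calendar makes this concrete: everyone was recruited within 19 days, so all participants pass through autumn, winter and spring together. The outcome includes mobility, food and consumption behaviours, which could plausibly change with the season.

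**Working it through.** **1. What one arm can identify.** Write I and C for the mean scores of the intervention and untreated control arms, with 0 for baseline, 5 for week 5 and F for a follow-up.

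- Effect at week 5: (I5 − I0) − (C5 − C0). All four means are observed.
- Effect at follow-up: (IF − I0) − (CF − C0). CF without treatment is not available once the waitlist arm may cross over. Those who decline the offer are a self-selected remainder.
- Follow-up against baseline in one arm: IF − I0 = remaining effect + drift common to everyone since baseline.
- Follow-up against week 5 in one arm: IF − I5 = change in the effect + common drift since week 5.

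Drift can work in either direction. It can hide a lost effect or make a retained one look lost. Selective attrition adds to both contrasts.

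**2. Calendar.** Recruitment ran from 1 to 19 September 2025. If the 5 weeks (35 days) start at recruitment (an assumption), week 5 falls on 6 to 24 October. The follow-ups then fall on about 6 to 24 November, January and April. This agrees with the timeline: "Data collection is scheduled to be completed in April 2026". Time since the intervention and calendar time are therefore almost fully confounded.

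**3. Inputs for the size of the problem.** The protocol gives no figure for the maintenance analysis, so there is none to reproduce. From the document: 694 recruited, 1:1 allocation, 30% attrition, two-sided α of 0.05, and a planning effect of 0.30 SD. Assumed: 30% attrition applies up to 6 months; the correlation r between two waves is 0.5 to 0.7; the SD is equal across waves.

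- Retained in the intervention arm: 694/2 × 0.7 = 242.9, about 243.
- SE of a paired change in SD units: √(2(1 − r)/n). For r = 0.5: √(1.0/243) = 0.064. For r = 0.7: √(0.6/243) = 0.050.
- P(significant) for a true change d: Φ(d/SE − 1.96) + Φ(−d/SE − 1.96).

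**4. Follow-up against week 5: probability that a true loss is not significant**

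| True loss | r = 0.5 | r = 0.7 |
|---|---|---|
| 0.10 SD (one third of 0.30) | 0.66 | 0.48 |
| 0.15 SD (half of 0.30) | 0.35 | 0.15 |

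For example, with d = 0.15 and r = 0.5: 0.15/0.064 = 2.34, and Φ(2.34 − 1.96) = 0.65, so the loss is missed with probability 0.35. If nobody dropped out (n = 347), the second row would be 0.20 and 0.05.

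**5. Follow-up against baseline: probability of a significant change when no effect remains but everyone drifts**

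| Common drift | r = 0.5 | r = 0.7 |
|---|---|---|
| 0.10 SD | 0.34 | 0.52 |
| 0.20 SD | 0.88 | 0.98 |

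The drift sizes are illustrative. The document gives no estimate of seasonal or retest change in the outcome.

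**The case against.** The follow-up is called naturalistic throughout, the secondary aims are introduced as exploratory, and between-group effect sizes are promised only at the primary endpoint. Cross-over of a waitlist arm is common practice. The choice of contrast, any margin and the rule of interpretation may stand in an analysis plan that is not shown.

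Much of this stands. The analysis can validly describe whether scores in the intervention arm persist, and the absence of a margin or a named contrast from an article is not a fault. But the naturalistic label describes the design, while the stated inference remains a test of intervention effects, and no detail elsewhere can restore the comparator.

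A reader might infer more than the document supports:

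- That a non-significant decline will be taken as maintenance. The protocol does not say so; step 4 of the working shows what would follow if it were.
- That the test succeeds more easily as data become sparser. This holds only for follow-up against week 5. Against baseline, fewer data make significance harder to reach.
- That attrition will be far heavier than 30%. That is the only attrition figure given.
- That the outcome is known to vary with season. Nothing in the document shows this; the point is that the design could not separate such variation from a lasting effect.

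**Conclusion.** The concern holds as a mismatch between the stated inference and the design. The Aims and Statistical methods sections promise a test of maintained effects, but the planned one-arm analysis can speak only of maintained scores.

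Under the assumptions shown, loss of half of the planned effect would go undetected with probability 0.35 to 0.15 in a comparison with week 5. A common drift of 0.20 SD with no effect left would be significant against baseline with probability 0.88 to 0.98. The identification argument does not depend on these figures; they show only how far each contrast could mislead. The randomised comparison at week 5 is untouched, so this should be corrected but does not threaten the trial's main result.

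**What to change.** - Replace the test of maintenance by estimation. From a mixed model, report change from week 5 and from baseline to 1, 3 and 6 months with 95% confidence intervals, for all participants randomised to the intervention.
- Label the results as uncontrolled, descriptive trajectories.
- In the Aims and Statistical methods sections, refer to maintained scores rather than maintained effects.
- Add to the Limitations section that no untreated comparator exists at follow-up, so that season, secular trend, repeated self-report and selective attrition cannot be separated from a lasting effect.
- If scores are to be called maintained, fix a margin in advance in SD units. It should not be a share of the observed week-5 difference, which is itself an estimate. Such a margin deals only with reading a non-significant change as no change. It does not remove drift, so it can support a statement about scores but not about effects.

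The cost is a change of wording and of reporting, and a weaker follow-up claim. With about 243 retained, the 95% interval for change from week 5 would be roughly ±0.13 SD (1.96 × 0.064) at r = 0.5 and ±0.10 SD (1.96 × 0.050) at r = 0.7. No change to the design, the data collection or the primary analysis is needed.

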### Study status and timeline

Ethical approval for the study has been obtained from the Swedish Ethical Review Authority (reference number 2025-03308-01). The first version of this study protocol was submitted in August 2025. Participant recruitment started on 1^st^ of September 2025 and was completed 19^th^ of September 2025 (N = 694). Data collection is scheduled to be completed in April 2026.

## Discussion

This project addresses climate change mitigation by focusing on individual-level behavioural change, while also recognizing its connection to broader societal transformation processes. Amid increasingly urgent climate challenges, it is essential to explore not only policy- and technology-driven solutions, but also strategies that empower individuals to take meaningful action. Recent large-scale surveys across Europe and North America consistently show that the general public express high levels of concern about climate change and a growing desire to engage in mitigation efforts [7,8]. These findings suggest a clear demand for practical guidance on how to adopt more sustainable lifestyles.

The goal of the current project is to develop and evaluate the effectiveness of a brief, internet-based intervention— “Sustainable Choices” —designed to promote CCMBs. A key strength of this approach is its scalability: the intervention is entirely self-guided and delivered online, making it accessible to a wide audience without the need for specialized personnel or infrastructure.

The “Sustainable Choices” project seeks to apply behavioural science principles to climate action. Importantly, the intervention is designed to prioritize high-impact behavioural domains—such as food choices, travel, energy use, and consumption—while also attending to individual psychological well-being. This dual focus reflects recent research suggesting that sustainable behaviours can, under the right conditions, co-benefit personal well-being, rather than burden it [16].

### Limitations

Several limitations apply to this study. Firstly, the choice of a waitlist condition does not allow for control of expectancy effects or unspecific intervention effects, such as exposure to novel content. Future evaluations should therefore consider study designs with more rigorous control conditions. Secondly, the current study uses a sample of voluntary individuals, most likely motivated for behavioural change. This recruitment strategy may introduce a selection bias in the sample and limits therefore generalizability to the broader public. Future evaluations of the ‘Sustainable Choices’ intervention should involve representative population samples. Thirdly, the follow-up period is limited to a half-year period, and thus long-term effects beyond this time frame will not be captured in the current study. Lastly, the current study makes use of self-report measures to capture primary and secondary outcomes. While there is some evidence that self-rating is associated with observable behaviours [29–31], the results warrant validation through study designs using objective measures.

